#### Cost calculation

Direct and indirect costs will be recorded with the help of a specific questionnaire, completed in a semi-structured interview. Costs relative to hospitalization, outpatient treatment, other interventions, medication, time spent by the family on treatment, informal care, interruption of schooling, and impact on parents’ professional activities will be taken into account.

### Outcomes

#### Primary outcome

The primary outcome is the evolution of BMI between inclusion and 12 months thereafter.

#### Secondary outcomes

Secondary outcomes are as follows:Change from baseline to months 12 and 18 in the overall patient’s clinical outcome (weight outcome, i.e., BMI > 10th percentile, presence of menstruation, GOAS category),Change from baseline to months 12 and 18 in the nature and seriousness of patient’s eating disorder symptoms (EDI-2 and EDDS scores),Change from baseline to months 12 and 18 in the nature and seriousness of patient’s other psychopathological symptoms (HADS, BDI-13, LSAS-CA-SR, MOCI, BVAQ-B, RSES, OSI, and C-SSRS scores),Change from baseline to months 12 and 18 in the nature and seriousness of parents’ psychopathological symptoms (HADS, BDI-13, BVAQ-B, RSES, ECI, EDSIS, and MIV-TIG scores),Change from baseline to months 12 and 18 in the quality of family relationships (FAD, SCORE-15, patients’ LEE scale, and parents’ FQ scores),Change from baseline to months 12 and 18 in the perceived quality of life (EDQOL and SOFAS scores for patients, WHOQOL-Bref, LHS, and CarerQOL-7D scores for parents),Number and duration of hospitalizations after inclusion,Patients’ and parents’ satisfaction (CSQ-8 and ECI scores) regarding the intervention,Cost of treatment between inclusion, 12 months, and 18 months thereafter.

Other measures will be explored as potential moderators or mediators of treatment outcome.

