#### Self-harm and suicidal behaviors

The Ottawa Self-Injury Inventory (OSI, [82]) is a self-report scale that evaluates non-suicidal self-injury (NSSI), which comprises an exploration of the reasons for engaging in NSSI and an assessment of addictive features. The scale comprises four factors: Internal Emotion Regulation, Social Influence, External Emotion Regulation, and Sensation Seeking, and a single Addictive feature factor.

The Columbia Suicide Severity Rating Scale (C-SSRS, [83]) is a clinician-rated questionnaire which can also be used as a self-report. The aim of this scale is to support suicide risk assessment by evaluating suicidal ideation as well as suicidal behavior. Four constructs are measured: Severity of Ideation, Intensity of Ideation, Suicidal Behavior, and Lethality.

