In order to compare financial costs between SFT and MFT, we will make an inventory of the treatments, and we will use the average cost for each ambulatory appointment (psychiatrist, psychologist, etc.) and the average treatment cost for hospitalization if necessary during follow-up; the sum will determine the total cost of treatment for each patient. Transport costs and other associated costs will not be estimated, as most patients live near the hospital. Costs for the two treatment groups will be compared using Fisher-Pitman’s test.

An analysis of quantitative variables (assessment scores) will be performed in the same way as for the principal criterion using an ANCOVA, with the value of each respective variable at admission, and for the status of treatment at inclusion (ambulatory care or hospitalization), as co-variables. Morgan- Russell GOAS scores (with the three following outcomes: good, intermediate, and poor) will be compared between SFT and MFT, using Cochran-Armitage’s tendency test. A measure of ordinal association (Somers’ *D*) will be calculated with a confidence interval of 95%. Amenorrhea and other qualitative variables will be compared using Fisher’s exact test. Additionally, for the clinical variables assessing outcome, analyses looking for moderators and treatment effect mediators will be carried out.

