#### Data collection and management

Data will be transferred to observation files as it is collected, whether it is clinical or para-clinical data. An electronic data capture system will be used for this trial. Data collected from the subjects will be directly captured into an electronic case report form (e-CRF). The investigator will log onto the clinical study website via a unique access code. Transmitted data will be made secure by a client certificate. Once a patient’s data is entered, the investigator will be able to sign and confirm his/her e-CRF. The system will support and validate data entry. Missing and erroneous data (e.g., out-of-range data) will be automatically detected and reported to the investigator for correction. In addition to this computerized data quality control, a manual quality check will be carried out by a clinical research assistant appointed by the trial Sponsor.

Essential research documents that come within the law on biomedical research will be archived by all parties for 15 years after the end of research.

All video recordings required for conducting supervision sessions will be destroyed at the end of the trial.

This trial is registered with the French National Commission for Data Protection and Liberties (CNIL) under Chapter IX of law no. 78-17 of 6 January 1978, modified by law no. 2016-41 of 26 January 2016, regarding the treatment of personal data for the purpose of scientific research in the health field.

The Sponsor has required an authorization for the processing of collected data, the use of patients’ identifying data (social security number, email address, videotaped sessions conducted with the informed consent of patients and parents), and access to the National Health Insurance Information System (SIIRNAM) database for the cost-efficiency analysis.

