In the same line, the inclusion and exclusion criteria that we have chosen are deliberately broad, to make this trial as naturalistic as possible and to ensure that our sample is representative of the patients we usually follow in our health- care facilities. We expect to define profiles of best responders for each technique. This would enable us to improve therapeutic indications and achieve greater and earlier efficacy, which is predictive of recovery and absence of chronicity.

This trial also presents some challenges we will have to consider. In order to obtain concrete and significant results, we have to recruit 150 patients and their families in a limited timeframe. If projections based on our regular active list of patients in the different study sites make us confident about an effective recruitment, we will consider the option to open a fourth study site in case of difficulties or unexpected delays.

We also wanted to conduct a follow-up evaluation to assess the maintenance of therapeutic results and to have a better evaluation costs in the long term. This will raise the problem of retention. The psychologists and psychiatrists in charge of evaluation are well versed in this problem and have experience in the management of follow-up evaluations of patients and families [86, 95]. Several strategies will be used to maintain the best retention rate possible, such as regular phone calls and communication with the coordinating psychiatrist. A large part of the evaluations will be possible online, with personal access codes, which will enable us to record important information, even if the patient and/or his/her family are not willing to come to the study site for assessment.

A last challenge concerns minimization of therapists’ bias. Indeed, all therapists involved in the trial are trained in both MFT and SFT. We expect to minimize this potential bias by proper training in the use of the therapeutic manuals, regular communication between all therapists, and sessions of supervision.

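### C-SSRS and OSI are planned only as change scores under the general ANCOVA rule, which can hide patients with new suicidal behaviour or self-injury

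*Protocol article*

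**What the plan says.** In the protocol article, Secondary outcomes places the two instruments in one list with depression, anxiety and self-esteem scales, "other psychopathological symptoms (HADS, BDI-13, LSAS-CA-SR, MOCI, BVAQ-B, RSES, OSI, and C-SSRS scores", each as a change from baseline to months 12 and 18.

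Statistical methods gives one rule for scores: "An analysis of quantitative variables (assessment scores) will be performed in the same way as for the principal criterion using an ANCOVA", adjusted for the baseline value and for inpatient or outpatient status at inclusion. Categorical outcomes are treated separately. The three-level GOAS outcome gets a trend test, and amenorrhea is named under the rule that "other qualitative variables will be compared using Fisher’s exact test". Suicidal behaviour and self-injury are not named there.

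Self-harm and suicidal behaviors says of the C-SSRS: "Four constructs are measured: Severity of Ideation, Intensity of Ideation, Suicidal Behavior, and Lethality". No total score is described for it, whereas totals are described for several other instruments, such as the LSAS-CA-SR, MOCI, SCORE-15 and LEE. The OSI "is a self-report scale that evaluates non-suicidal self-injury (NSSI"; its listed factors concern the functions of self-injury and its addictive features.

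**The concern.** Whether a patient shows suicidal behaviour, or injures herself or himself, is closer to a yes/no event than to a point on a scale. If most patients have none, the data are sparse and a difference in mean change answers the wrong question. It reports net movement, so a patient who stops and a patient who starts cancel. A reader who wants to know whether either therapy is followed by new cases cannot tell from it.

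Two features of the instruments as described add to this. With four constructs and no total, the C-SSRS quantity that enters the ANCOVA is not identified. And if the OSI factors describe why a patient self-injures, a patient with no self-injury at baseline has no obvious baseline value. That second step is an inference from the article's short description. It would mean that new cases fit the planned model worst.

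At stake is the visibility of a serious secondary outcome when the two therapies are compared.

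**Working it through.** **Inputs.** The article gives no event rate and no SD for either instrument, so everything below is illustration. The 60 per arm comes from Sample size: 75 randomised per arm with 20% dropout, 75 × 0.80 = 60. The 12 positives per arm, the changes, the ideation scale, the SDs and the event rates are assumptions.

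**1. Cancellation.** Code behaviour as 1 (present) or 0 (absent), with 12 of 60 positive at baseline in each arm.

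| | MFT | SFT |
|---|---|---|
| Positive at baseline | 12/60 | 12/60 |
| Resolved | 6 | 0 |
| New | 6 | 0 |
| Positive at follow-up | 12 − 6 + 6 = 12/60 | 12/60 |
| New among baseline-negative | 6/48 | 0/48 |

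The ANCOVA difference is (follow-up mean MFT − follow-up mean SFT) − slope × (baseline mean MFT − baseline mean SFT) = (0.20 − 0.20) − slope × (0.20 − 0.20) = 0, whatever the slope. Care status is taken as balanced between arms.

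**2. Counting patients without a baseline split.** Any event at follow-up is 12/60 against 12/60: risk difference 0, Fisher p = 1. A plain count is not enough.

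**3. Counting with a baseline split.** Among baseline-negative patients, 6/48 against 0/48 is a risk difference of 12.5 percentage points. Two-sided Fisher p = 2 × C(48,6)/C(96,6) = 2 × 12,271,512/927,048,304 = 0.0265. Among baseline-positive patients, 6/12 against 12/12 still positive shows the resolution. The split uses a pre-randomisation variable, so each stratum is still a randomised comparison.

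**4. A graded score.** Suppose w of 60 patients in one arm worsen by 4 points on an assumed 0–5 ideation score.

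- Shift in the arm mean: w × 4/60, so 0.20 for w = 3 and 0.33 for w = 5.
- Average improvement in the other patients that cancels it: w × 4/(60 − w), so 12/57 = 0.21 and 20/55 = 0.36.
- Power of a two-sided 5% comparison, Φ(shift/(SD × √(2/60)) − 1.96), for SD from 2.0 down to 1.0: 0.08 to 0.19 (w = 3) and 0.15 to 0.45 (w = 5).

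**5. Power of the replacement.** Fisher's exact test, two-sided 5%, 60 per arm: 0.15 for 2% v 8%, 0.19 for 3% v 10%, 0.33 for 5% v 15%, 0.63 for 5% v 20%. Restricting to baseline-negative patients leaves fewer per arm, so power at the same rates will generally be lower still. The event analysis is therefore no strong test either.

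**The case against.** The strongest reply is that the article never names ANCOVA for the C-SSRS. It confines ANCOVA to quantitative variables and sends qualitative ones to Fisher's exact test, so an occurrence variable for suicidal behaviour could already fall there. The choice by construct may also sit in an analysis plan that is not shown. This stands in part: the Fisher rule leaves room for the right analysis. But the article specifies both instruments as scores with change from baseline, it singles out categorical outcomes where it wants them, and it names no event outcome here. On a plain reading they go to ANCOVA.

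It is also fair that the example is hand-built, with exact cancellation in one arm and no movement in the other, and that Fisher's test has little power for rare events. Both points stand, and they limit the claim to visibility of cases.

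A reader might infer more from three other places, and the article does not support it.

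- **Mode of administration.** The statement that the C-SSRS "is a clinician-rated questionnaire which can also be used as a self-report" describes what the instrument permits. It does not show that this trial mixes modes, still less by attendance. The OSI is self-report for everyone.
- **Online completion.** "A large part of the evaluations will be possible online, with personal access codes" names neither instrument.
- **Unread answers.** The check under which "Missing and erroneous data (e.g., out-of-range data) will be automatically detected and reported to the investigator for correction" is not the only safeguard described. The article also provides investigator sign-off of the e-CRF, a manual quality check, a coordinating psychiatrist and regular phone calls. Handling of alarming answers is something a condensed article commonly leaves to the full protocol, so silence on it is no finding.

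**Conclusion.** The concern holds as a point about analysis choice. The article specifies the C-SSRS and OSI only as change scores, under a general ANCOVA rule that suits occurrence data badly and can return exactly 0 when new onset differs by 6/48 against 0/48. This rests on two assumptions: that these events are sparse in this population, and that the general score rule applies to both instruments as written.

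The size is modest. It is a secondary outcome, and the primary BMI analysis and the non-inferiority decision do not depend on it. With power of about 0.15 to 0.63 in the scenarios tried, the corrected analysis would be descriptive and would often miss a true excess as a formal test. Its value is that new cases are counted and shown.

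**What to change.** In Secondary outcomes and Statistical methods, define two qualitative outcomes: any suicidal behaviour (C-SSRS) and any self-injury (OSI) since the previous assessment, at months 12 and 18. For each:

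- give the number of patients with an event and the number assessed, per arm;
- split by whether the behaviour was present at baseline, so that new onset among baseline-negative patients is shown;
- give the risk difference with 95% CI, and Fisher's exact test as already planned for qualitative variables;
- state that the comparison is descriptive.

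ANCOVA may stay for ideation scores, with the score named. Because assessments are at baseline, 12 and 18 months, the two look-back periods are 12 and 6 months and should be labelled so. The team should confirm which OSI item records occurrence, since the article describes only its factors.

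The cost is a few sentences of analysis text and one small table per outcome, with no new instrument, visit or test. The downside is low power for rare events. The article reports recruitment as ongoing, so on its account the wording can be settled before analysis.

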### Statistics

#### Sample size

One hundred and fifty patients and their parents will be recruited.

Power calculation for the primary endpoint of this study is based on the assumption that MFT is not less effective than SFT if a minimal clinical difference of 0.75 kg/m^2^ in mean change of BMI between baseline and 12 months follow-up cannot be shown between groups. The principal judgement criterion*,*
*i.e*., the variation of BMI 12 months after the beginning of treatment, was established after having reviewed family therapy trials and recent trials on AN, whether in the field of family therapy or in other therapeutic trials ([85]). The non-inferiority margin of 0.75 kg/m^2^ is based on clinical experience and is consistent with the scientific literature. The standard deviation of the BMI variation is estimated at 1.45 [85, 86].

Consequently, we determined the size of the sample for a unilateral Student’s *t* test with a significance of 2.5% and a power of 80% with the non-inferiority margin clinically determined for a minimum BMI difference of 0.75 kg/m^2^, assuming the standard deviation to be 1.45.

This procedure led to a required sample size of 60 patients per group. Assuming that the dropout rate is 20% [86], we calculated a sample size of 75 patients per treatment group.

With a total active file of more than 500 patients in the three study sites, we expect to complete the recruitment of 150 eligible patients in 2 years.

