#### Multi-family therapy (MFT)

Each session will involve 5 to 7 families of patients suffering from AN including the parents and non-systematically the siblings. Sessions will last 3 h.

 MFT follows the integrative model practiced by [name], which includes elements from the Maudsley approach [37]. MFT will be conducted according to three main dimensions: psychoeducative dimension, support group dimension and family therapy dimension. Four main themes are addressed: (1) understanding and managing AN, (2) family relations and family identity, (3) overcoming social isolation, (4) values, beliefs, and perceptions.

In addition to the general objectives of SFT, objectives of MFT include the following:To improve communication and interaction between the different family members,To overcome the sense of isolation and the feeling of shame, by creating a sense of solidarity between families facing the same illness,To foster mutual learning and support, by sharing experiences,To develop competencies to fight against the pathology,To develop parental empathy toward the patient, to decrease attitudes of hostility and rejection,To maintain an attitude of hope and realistic optimism,To avoid stagnation in relationships between carers and patients.

While some of the objectives are achieved naturally by the structure and dynamics of the group, other objectives are encouraged by specific interventions and therapeutic strategies and techniques. MFT uses a wide range of techniques and approaches, reflecting the conceptual diversity that underlies it. MFT tools are based on cognitive behavioral (psychoeducational approach), systemic (group approach and family therapy), psychodynamics (differentiation process through identification with other families, learning by analogy) and medical family therapy concepts and practices (adaptation to processes of illness). As described by some authors [28], this mix of practices creates a “greenhouse effect” that promotes openness and catalyzes change. MFT is based on the hypothesis that the intensity of the program creates opportunities for each family to witness extreme emotions and receptiveness [24, 28]. This process is an important factor in the evolution of family dynamics, allowing families to change some of the behaviors that had so far restricted the scope for change and growth.

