#### Statistical methods

Regarding the primary objective, we will compare the evolution of BMI between baseline and after 12 month follow-up in the MFT and SFT groups, using an analysis of covariance (ANCOVA) with BMI at inclusion as a pre-specified co-variable, as well as inpatient status versus outpatient care.

As recommended by the Consolidated Standards of Reporting Trials (CONSORT) guidelines for non-inferiority clinical trials [87], the confidence interval of the intergroup difference of the principal criterion thus obtained will be calculated and represented graphically. The decision to conclude in favor of the non-inferiority of MFT in comparison with SFT will be made only if the upper boundary of the confidence interval is below the chosen non-inferiority threshold of 0.75 kg/m^2^.

It is recommended to carry out a double approach, intention to treat (ITT) and per protocol (PP), for the analysis of the principal criterion in cases of non-inferiority clinical trials [88], as the non-observation of a randomized treatment could reduce differences in efficacy of the two treatments and could therefore bias the trial results. The ITT analysis will include all patients randomized in their randomization group, whatever the treatment they have actually received. The PP analysis will only include patients who have followed at least three sessions without any treatment change or protocol violation. Then, in a sensitivity analysis, we will add age and illness duration to the models as co-variables, as they are important prognostic factors. Finally, if non-inferiority has been demonstrated, the superiority of the MFT treatment over the SFT treatment will be assessed in ITT.

Regarding the secondary outcomes, financial cost and satisfaction will be analyzed for the superiority of the MFT treatment over the SFT treatment. We will compare subject and parent satisfaction with the treatments (as evaluated by the CSQ-8 and ECI) at 12 months using an ANCOVA, with the status of treatment is a co-variable at inclusion (outpatient or inpatient) as a pre-specified co-variable.

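### MFT is given in groups of families, but the sample size and primary ANCOVA treat all patients as independent; any positive within-group correlation makes the non-inferiority interval too narrow

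*Protocol article*

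**What the plan says.** **Delivery.** Under Multi-family therapy (MFT), the article says: "Each session will involve 5 to 7 families of patients suffering from AN including the parents and non-systematically the siblings". Under Systemic single-family therapy, the unit treated is one family. Therapist dyads deliver both treatments (Common characteristics of interventions). The MFT section expects part of the benefit to come from the group: "While some of the objectives are achieved naturally by the structure and dynamics of the group". The same sentence adds that other objectives are pursued through specific techniques.

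**Sample size.** The calculation is a one-sided Student t test "with a significance of 2.5% and a power of 80% with the non-inferiority margin". Its inputs are a margin of 0.75 kg/m² ("The non-inferiority margin of 0.75 kg/m^2^ is based on clinical experience") and one standard deviation ("The standard deviation of the BMI variation is estimated at 1.45"). "This procedure led to a required sample size of 60 patients per group", raised to 75 for 20% dropout. There is no ICC and no design effect.

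**Analysis.** Statistical methods fixes the primary comparison, "using an analysis of covariance (ANCOVA) with BMI at inclusion as a pre-specified co-variable", with inpatient or outpatient status as the other covariate. Non-inferiority is declared if one confidence limit clears 0.75. The same form of ANCOVA is used for the quantitative secondary outcomes. The article mentions no group term, random effect or robust variance, and gives no reason to treat MFT patients as independent.

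**The concern.** The design is partially nested. The 75 MFT patients form about 75/7 = 11 to 75/5 = 15 groups, while SFT patients are treated singly. Families in one MFT group share sessions, therapists and each other's company for a year, so some correlation in outcome is plausible. If it is positive, the MFT mean is less precise than a patient-level model reports.

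The direction of the error matters here. The only confirmatory decision is whether one confidence limit clears the margin, so an interval that is too narrow favours declaring MFT non-inferior, which is the trial's hypothesis. Running both ITT and per-protocol analyses gives no protection, because both use the same model.

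**Working it through.** **Inputs from the article:** one-sided 2.5%, power 80%, margin 0.75, SD 1.45, 60 analysed per arm, 20% dropout, groups of 5 to 7. **Assumed:** true difference 0; ICC 0.01 to 0.10, because none is given.

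**1. The plan's own figure.** Normal approximation: n = 2 × (1.96 + 0.842)² × 1.45² / 0.75² = 58.7 per arm. With the noncentral t distribution, power is 79.6% at 59 and 80.2% at 60. Dropout: 60 / 0.8 = 75. The stated 60 and 75 reproduce under independence, with a reserve of only 0.2 percentage points.

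**2. Group size for the check.** Twelve groups would recruit 75/12 = 6.25 families each, inside the stated 5 to 7. After 20% dropout that leaves 6.25 × 0.8 = 5 analysed. So m = 5, with 12 groups.

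**3. Effect of grouping.** Only the MFT arm is inflated:

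- Design effect DE = 1 + (m − 1) × ICC.
- True SE = 1.45 × √[(DE + 1)/60]; under independence it is 1.45 × √(2/60) = 0.265.
- SE ratio = √[(DE + 1)/2].
- One-sided error of the ordinary analysis at the margin = 1 − Φ(1.96 / SE ratio).
- Power of a group-aware analysis: noncentral t with noncentrality 0.75 / true SE and Satterthwaite degrees of freedom from 12 groups and 60 SFT patients.

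At ICC 0.05, for example: DE = 1 + 4 × 0.05 = 1.20; SE ratio = √1.10 = 1.049; error = 1 − Φ(1.869) = 3.1%; true SE = 0.278, noncentrality 2.70, df about 33.

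| ICC | DE | SE ratio | Error, ordinary | Power, ordinary | Power, group-aware |
|---|---|---|---|---|---|
| 0.01 | 1.04 | 1.010 | 2.6% | 80% | 78% |
| 0.02 | 1.08 | 1.020 | 2.7% | 80% | 77% |
| 0.05 | 1.20 | 1.049 | 3.1% | 79% | 74–75% |
| 0.10 | 1.40 | 1.095 | 3.7% | 78% | 70% |

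The power of the ordinary analysis is from simulation with an unadjusted t test. Simulated error rates agree with the formula (3.1 to 3.2% at ICC 0.05, 3.7% at 0.10). The group-aware analysis held its error near 2.5% in simulation.

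**4. Sensitivity to group size.** After 20% dropout, groups of 5 to 7 average 4 to 5.6 analysed. At ICC 0.05 the ordinary error is 2.9% (m = 4) to 3.2% (m = 5.6); at ICC 0.10 it is 3.4% to 3.9%. With a full 7 analysed per group it would be 3.4% and 4.3%.

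**5. Baseline adjustment.** The sample size takes no credit for it. If the covariates explained 10% of the variance (assumed), the SE would shrink by a factor √0.90 = 0.949. At ICC 0.05 the net SE ratio against the planning value is 1.049 × 0.949 = 0.995, so power is recovered apart from the cost of fewer degrees of freedom. At ICC 0.10 it is 1.095 × 0.949 = 1.039. The error rate is not repaired, because adjustment shrinks the reported and the true SE together. Simulating the ANCOVA with such a covariate left the error at about 3.0% (ICC 0.05) and 3.6% (ICC 0.10).

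**The case against.** The strongest reply is that the effect may be small. No ICC is given, and at 0.01 to 0.02 the ordinary analysis has an error of 2.6 to 2.7%. The endpoint is BMI, whereas the objectives listed specifically for MFT concern communication, isolation, empathy and hope. Both arms also receive individual multidisciplinary care aimed at eating symptoms and starvation. This stands: the size is unknown. For the same reason, a reader might infer that the article makes group dynamics the active ingredient for weight; the text does not say so, and the sentence on group structure goes on to credit specific techniques as well.

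Two further points deserve weight. Covariate adjustment can offset the loss of power, though not the excess error. Centre stratifies the randomization but is not in the ANCOVA, so any centre effect makes the reported SE somewhat conservative.

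It may also be said that a condensed article leaves random effects and degrees of freedom to the analysis plan. That would answer silence. Here the article names the model, its covariates, the sample-size method and the decision rule, and an analysis plan that follows it inherits the independence assumption.

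**Conclusion.** The concern holds in conditional form. The sample size and the primary model both assume independence in a design where one arm is treated in groups. For any positive within-group correlation in BMI change, the stated interval is too narrow, and it errs towards non-inferiority. With 12 analysed groups of 5, the excess error is slight at ICC 0.02 and becomes material from about 0.05.

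Two stronger readings are not supported. The first is that the 80% power is simply not delivered: without an ICC this cannot be stated as fact, and under the ANCOVA as written power barely moves. The second is that excess error and lost power occur together in full. They are alternatives: keep the ANCOVA and the cost is mainly false non-inferiority; account for groups and the cost is mainly power.

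The figures assume equal groups, fixed membership, a common total SD of 1.45 and no therapist effect. Correlation by therapist dyad would add to the problem.

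**What to change.** - Record MFT group and therapist dyad in the e-CRF, preferably while sessions are running.
- For the ITT and per-protocol non-inferiority intervals and the quantitative secondary outcomes, replace the ANCOVA by a partially nested mixed model. Keep the planned covariates, add a random intercept for MFT group in the MFT arm only, treat each SFT family as its own unit, and use Satterthwaite or Kenward-Roger degrees of freedom.
- Examine therapist dyad, which spans both arms, in a sensitivity analysis.
- The article does not say whether group membership is fixed. If it is not, adapt the group term, since a simple random intercept may then fit poorly.
- Restate the power in Sample size over an assumed ICC range such as 0.01 to 0.10.

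**Cost:** wording, two data fields, a slightly wider interval and a less favourable stated power. The 150 patients stay. This makes the power statement honest but does not restore 80%. By the normal approximation without baseline adjustment, restoring it for analysed groups of 5 to 7 would take about 82 to 85 recruited per arm at ICC 0.05 and 89 to 97 at ICC 0.10. If the ICC is near zero, the model costs only a point or two of power.
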